### Secondary outcomes

2.10

National Institute of Health Stroke Scale (NIHSS)^[20]^ scores for neurological deficit, Modified Barthel Index (MBI)^[21]^ scores for activities of daily living (ADL), TESS^[22]^ scores for side effects of treatments, diagnosis and evaluation criteria of TCM for stroke (try out)^[23]^ scores for curative effects of stroke, and clinical global impression (CGI)^[24]^ scores for synthesize effect before and the 2nd, 4th, 8th, 12th week of treatment, and 24th week of follow-up. Patients’ diary for tracking their mood, sleep, diet, medications, adverse events, and others during the research was maintained. All the dropouts and causes will be documented in case report form (CRF).

### Estimation of sample size

2.11

Based on the previous pilot study,^[25]^ the mean change in HAMD-17 before and after treatment was used as the indicator for the efficacy evaluation in the calculation of the sample size. Results from our previous studies showed that the mean HAMD-17 scores change was 10.49 ± 4.55 after acupuncture treatment and 10.24 ± 4.46 after fluoxetine treatment. Thus, we performed a noninferiority test to calculate the appropriate trial sample size with 90% power, beta of 0.1, alpha of 0.05. The results showed that a clinically important difference can be detected by a sample size of at least 84 in each group. This number was then increased to 104 per group to allow a predicted 20% dropout rate. We will plan to enroll in all 208 participants in this study.

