### Study design

2.1

This is a multicenter, central-randomized, single-blind, sham-controlled, noninferiority clinical trial. In all, 208 participants will be randomized into 2 groups at a ratio of 1:1. Participants in the treatment group will be treated with traditional acupuncture and placebo medicine. Participants in the control group will be treated with sham-acupoint acupuncture and medicine (fluoxetine hydrochloride tablets).

The whole study period is 25 weeks, including 1-week baseline observation, 12-week treatment, and 12-week follow-up. Patients will be evaluated with scales for clinical efficacy before and the 2nd, 4th, 8th, 12th week of treatment, and 24th week of follow-up, and monitored by proton magnetic resonance spectroscopy (^1^H-MRS) and serum for acupuncture mechanisms before and the 12th week of treatment (Fig. 1).

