### Statistical analysis

2.13

Data analysis will be based on intention-to-treat analysis (ITT) and/or per-protocol analysis (PP) principle in the light of missing data. We will also evaluate the group effect by comparing the analysis results between the above 2 data sets to evaluate robustness of our analytical results.

All data will be analyzed using SPSS19.0 (v19.0, SPSS Inc., Chicago, IL) in the China Academy of Chinese Medical Sciences (CACMS). A *P* value <.05 will be considered as significant. Descriptive statistics will be performed with mean, standard deviation (SD), maximum, minimum, and so on by groups and time.

Baseline characteristics of patients will be summarized by groups and compared with chi-square for categorical variables, and 2-sample *t* tests (normal distributions) or Wilcoxon rank-sum test (non-normal distributions) for the continuous variables. Primary and secondary outcomes according to the measurement times are applicable to univariate repetitive measurement deviation analysis or 2-sample *t* tests, or Wilcoxon rank-sum test. If there is a violation of distribution assumption, appropriate transformation will be used.

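### The noninferiority sample size (84 per group, 90% power) is given without a margin, a side for alpha or an assumed true difference, so it cannot be reproduced or tied to a decision threshold

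*Protocol article*

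**What the plan says.** Section 2.1 fixes the design: "This is a multicenter, central-randomized, single-blind, sham-controlled, noninferiority clinical trial".

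Section 2.11 sizes it on HAMD-17 change: "the mean change in HAMD-17 before and after treatment was used as the indicator for the efficacy evaluation". The pilot input is "the mean HAMD-17 scores change was 10.49 ± 4.55 after acupuncture treatment and 10.24 ± 4.46 after fluoxetine treatment". The calculation is described in one sentence: "we performed a noninferiority test to calculate the appropriate trial sample size with 90% power, beta of 0.1, alpha of 0.05". Its result is that "a clinically important difference can be detected by a sample size of at least 84 in each group", raised to 104 per group for 20% dropout.

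The article gives no noninferiority margin in any section. It does not say whether alpha 0.05 is one- or two-sided, or whether the calculation assumed a true difference of 0.25 or of 0.

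On analysis, section 2.13 says that a P "value <.05 will be considered as significant". Section 2.13.1 reads a significant group effect as showing that HAMD-17 and SDS scores differ between groups. Neither section compares a confidence limit with a margin.

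**The concern.** A noninferiority sample size is determined by the margin, the one-sided alpha, the SD and the assumed true difference. Section 2.11 prints the SDs, the power and an alpha, but not the margin, which defines the hypothesis. A reader cannot tell what loss of HAMD-17 improvement against fluoxetine would still count as noninferior, and a margin not fixed in print could be chosen after the data are seen.

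The closing claim about detecting a clinically important difference is superiority wording, without a number, attached to a noninferiority calculation. The P<.05 difference tests do not supply the missing criterion: a non-significant difference does not show noninferiority. As written, the 90% belongs to no planned test.

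The assumed difference matters as well. If the pilot's 0.25-point advantage for acupuncture was built into the calculation, 90% is not the power under equal efficacy, which is the usual reference case for a noninferiority design.

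**Working it through.** **Inputs (section 2.11).** SDs 4.55 and 4.46; means 10.49 and 10.24; n = 84 per group; power 90%; alpha 0.05, side not given. Normal approximation throughout.

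**Derived quantities.**
- Pilot difference: d = 10.49 − 10.24 = 0.25 in favour of acupuncture.
- Pooled SD = √[(4.55² + 4.46²)/2] = 4.505.
- SE of the difference with 84 per group = 4.505 × √(2/84) = 0.695.

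**Can 84 be reproduced?** The formula is n = 2·SD²·(z_α + z_β)² / (M + d)², where M is the margin and d the credited advantage. M is not printed, so the answer is no. The formula can only be solved backwards: M = (z_α + z_β)·SE − d, with z_β = 1.2816.

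Power at true equality is then Φ(M/SE − z_α):

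| One-sided alpha | Advantage credited | Implied margin | Power at true equality |
|---|---|---|---|
| 0.025 | 0.25 | 3.2415 × 0.695 − 0.25 = 2.00 | 82% |
| 0.025 | 0 | 2.25 | 90% |
| 0.05 | 0.25 | 2.9264 × 0.695 − 0.25 = 1.78 | 82% |
| 0.05 | 0 | 2.03 | 90% |

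The 82% is the same at either alpha because the margin is back-solved: 1.2816 − 0.25/0.695 = 0.922, and Φ(0.922) = 0.822.

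**Does the value 84 reveal which inputs were used?** It does not. Only the sum M + d enters the formula.
- M = 2.0, d = 0.25, one-sided 0.025: n = 84.25.
- M = 2.25, d = 0, one-sided 0.025: n = 84.25, identical.
- M = half an SD, d = 0, one-sided 0.025: n = 2 × 10.507/0.25 = 84.06.
- M = 2.0, d = 0, one-sided 0.05: n = 86.9. With 84 per group, power is 89.1%.

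All these margins are assumptions. For scale, M = 2.0 with d = 0 at one-sided 0.025 would need 106.6, so 107 per group; 84 would then give 82.0%.

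**The planned difference test.** If the true difference were the pilot's 0.25, a two-sided 0.05 test with 84 per group would have power Φ(0.36 − 1.96) + Φ(−0.36 − 1.96) = 0.055 + 0.010, about 6.5%. The 90% clearly does not describe that test.

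**If 0.05 was used one-sided and alpha is then set at one-sided 0.025.** With the margin kept, power at equality becomes Φ(2.034/0.695 − 1.960) = Φ(0.966) = 83% for the uncredited margin, or Φ(1.784/0.695 − 1.960) = Φ(0.607) = 73% for the credited one.

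**The case against.** A condensed article may leave detail to the full protocol or the SAP, neither of which is shown, and the margin may be stated there. This has limited force. Section 2.11 is a complete sample-size paragraph with means, SDs, power, beta, alpha, dropout and n, and it omits the one input that defines the hypothesis. What it does print, the detection claim, is wrong for the stated design, and sections 2.13 and 2.13.1 set out a decision rule that is not one of noninferiority.

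A reader might go further and infer that the calculation credited acupuncture with the pilot's 0.25 points, so that true power is about 82%. The inference is tempting: both pilot means are listed, the next sentence begins with Thus, and a round margin of 2.0 with the credit gives 84.25. The document does not support it. Listing the means is equally consistent with using only the SDs, or with showing similar efficacy as the reason for a noninferiority design. Margin 2.25 without credit gives the same 84.25, and half an SD without credit gives 84.06, slightly closer to 84. No fit to 84 can separate these cases. That part of the objection stands: no printed figure is shown to be miscalculated, and 82% is only the lower end of a range.

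**Conclusion.** The point holds as a failure to specify the noninferiority calculation, together with wording that contradicts the design. The 84 per group and the 90% power cannot be verified, and the plan as printed contains no threshold for concluding noninferiority.

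The same text is compatible with margins from 1.78 to 2.25 HAMD-17 points and with power at true equality of about 82% or about 90%, that is, a type II error of 18% or 10%. These figures rest on the pooled pilot SD of 4.505, 84 evaluable per group, the normal approximation and the two candidate assumptions about the 0.25-point credit. Which assumption was used is not known, so 82% should not be reported as the trial's power.

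**What to change.** In section 2.11:

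1. State the HAMD-17 margin actually used, in points.
2. State alpha as one-sided 0.025, equivalent to a two-sided 95% confidence interval.
3. State the true difference assumed in the calculation.
4. Report the power that 84 evaluable per arm gives at a true difference of 0 with that margin and alpha, and restate the 90% if it is lower.
5. Replace the sentence on detecting a clinically important difference with the noninferiority criterion: the confidence limit for the between-group difference in HAMD-17 change compared with the margin.

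The margin should be the one already used, not one back-solved from 84.

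The cost is one rewritten paragraph and no extra patients. The drawback is that the stated power may become less favourable: about 82% if the advantage was credited, and 83% or 73% (without or with the credit) if the calculation used a one-sided 0.05.

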### Randomization and blinding

2.12

After recruitment, the Central Randomization System performed by the China Academy of Chinese Medical Sciences (CACMS) would be used to randomize patients who meet the eligibility criteria into 2 groups at a ratio of 1:1. Every center will compete for the random numbers from random sequence generated by the Central Randomization System. Each subject will be registered with a unique ID. After the clinical screening and getting the informed consent forms, subjects will be assigned to experimental group (verum acupuncture + placebo pills) and control group (sham-acupoints acupuncture + fluoxetine) randomly. Each subject will receive the similar the number of acupoints and medications, as well as the stimulating amount of needling. Both groups will be in the package with the same looking and similar inner feeling, whereas all subjects will not be aware of the grouping.

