### Primary outcomes

2.9

The HAMD-17 and Se1f-rating Depression Scale (SDS)^[19]^ scores for depression state before and the 2nd, 4th, 8th, 12th week of treatment, and 24th week of follow-up. The diversity of choline-containing compounds (Cho), N-acetylaspartate (NAA), myoinositol (MI), glutamine and glutamate complex (Glx), creatine (Cr), Cho/Cr, Cho/NAA, and Cr/NAA in bilateral dorsolateral prefrontal cortex and anterior cingulate cortex. The levels of 5-hydroxytryptamine (5-HT), norepinephrine (NE), dopamine (DA), brain-derived neurotrophic factor (BDNF), intereukin (IL)-4, IL-6, IL-10, IL-18, IL-1β, and tumor necrosis factor alpha (TNF-α) in serum before and the 12th week of treatment.

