### Quality control

2.14

The reasons of dropouts or withdrawals throughout the treatment and follow-up periods will be fully recorded. To ensure trial quality, the quality monitors will verify all the process details at regular intervals and check the authenticity of the data. Moreover, a third party (CACMS) will be invited to manage the data independently.

Because differences among centers can cause bias, to reduce the bias, the evaluation of the rating scales in every subcenter will be executed by 2 psychiatrists who have been trained with the same criterion of evaluating. Also, there are 6 psychiatrists in total. All acupuncturists will receive special training about the study and manipulations including locations of acupoints, depth, and direction of needling, frequency of lifting and inserting, and so on before recruitment. To record the attendance and compliance, we make record cards for patients which cover date of treatment, personal information, and their signatures after every treatment.

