Acupuncture has been widely used and received in clinical practice in China.^[35]^ Patients in China are usually familiar with acupuncture, and expect to receive acupuncture treatments when they participate in this kind trial. Apart from this, because acupuncture is often regarded as an invasive operation,^[36]^ it is difficult to design a nonpenetrating sham acupuncture, which does not produce any physiological effects,^[37]^ and would not be experienced and recognized by patients at home. However, to improve subject compliance and achieve blinding, sham acupuncture will be necessary in the control group, whereas placebo pills will be adopted in experimental group in a high-quality RCT. So, in this study, sham acupuncture and placebo pills are applied simultaneously to eliminate the placebo effect. We choose needling at blunt acupoints as sham acupuncture without effect on depression, based on literatures^[18]^ and clinical experience.

Although studies have showed the efficacy of acupuncture for PSD,^[38,39]^ multicenter and large-sample RCTs are still lacking, and also the relevant mechanism research, which would be helpful to provide high-quality evidence for evaluation of acupuncture on PSD. Our protocol was designed through an extensive discussion by reference to several previous related studies.^[40–42]^ We try our best to attempt to minimize the biases that may influence study results. Finally, we intend to demonstrate the hypothesis that acupuncture as an alternative may be validated for PSD.

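### The trial is single-blind with subjects as the only party stated to be blinded, and nothing provides for masking the psychiatrists who rate HAMD-17, the outcome on which the trial was sized

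*Protocol article*

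**What the plan says.** Section 2.1 (Study design) states: "This is a multicenter, central-randomized, single-blind, sham-controlled, noninferiority clinical trial". The abstract uses the same single-blind label.

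Section 2.12 (Randomization and blinding) names one blinded party: "whereas all subjects will not be aware of the grouping". The Discussion explains the sham and placebo from the subjects' side: "to improve subject compliance and achieve blinding, sham acupuncture will be necessary in the control group". It does not mention raters.

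Section 2.14 (Quality control) says who scores the scales: "the evaluation of the rating scales in every subcenter will be executed by 2 psychiatrists who have been trained with the same criterion of evaluating". The reason given is to limit differences between centres.

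HAMD-17 is a primary outcome in section 2.9, together with the SDS, brain metabolites and serum markers. Section 2.11 makes it the basis of the sample size: "the mean change in HAMD-17 before and after treatment was used as the indicator for the efficacy evaluation".

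Section 2.7.1.1 places verum needles in the face and scalp as well as the body. Section 2.7.2.1 places sham needles in the limbs on the affected side.

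**The concern.** HAMD-17 is scored by an observer and involves judgement. An observer who knows the arm may score differently in the two arms, and that difference passes straight into the treatment contrast. Randomization does not protect against it, and analysis cannot reliably remove it afterwards.

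The stated safeguard addresses a different problem. Training to a common criterion reduces differences between raters and between centres. It does not stop a well-trained rater who knows the allocation from rating the two arms differently.

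Unmasking is a practical possibility here. The tablets match, but the needle sites do not. Section 2.8 lists bleeding under the skin as a likely effect of needling, so a mark on the face, or a patient's remark about a needle there, could reveal the arm.

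In a noninferiority trial, a shift toward the experimental arm raises the chance of declaring noninferiority when it is false. A shift the other way costs power.

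**Working it through.** **Inputs**
- Pilot changes in HAMD-17 (section 2.11): "10.49 ± 4.55 after acupuncture treatment and 10.24 ± 4.46 after fluoxetine treatment". The difference is 10.49 − 10.24 = 0.25 in favour of acupuncture.
- Pooled SD = √((4.55² + 4.46²)/2) = 4.505.
- 84 evaluable per arm, 90% power, alpha 0.05 with sidedness not stated (section 2.11).
- Noninferiority margin: not stated. Size and direction of any rater bias: not stated. Shifts of 0.25, 0.5 and 1 HAMD-17 point are assumed.

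**Step 1. The plan's own figure.** Without a margin, 84 per arm cannot be reproduced forward. Solving backwards:

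SE = 4.505 × √(2/84) = 0.695

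implied margin = (z(1−α) + z(0.90)) × SE − assumed true difference

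| One-sided α | True difference 0 | True difference +0.25 |
|---|---|---|
| 0.025 | (1.960 + 1.282) × 0.695 = 2.25 | 2.00 |
| 0.05 | (1.645 + 1.282) × 0.695 = 2.03 | 1.78 |

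The implied margin is about 1.8 to 2.25 points. As a forward check, a margin of 2, a true difference of +0.25 and one-sided 0.025 give 85 per arm, close to 84. That margin remains an inference.

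**Step 2. False noninferiority.** Let the true deficit equal the margin, and let ratings shift by b toward acupuncture. Then

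P(declare noninferiority) = Φ(b/SE − z(1−α))

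The margin cancels, so this result does not depend on its exact value. For b = 0.5 at one-sided 0.025: Φ(0.719 − 1.960) = 10.7%.

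**Step 3. Power.** At the design alternative, a shift of b against acupuncture gives power = Φ(z(0.90) − b/SE). For b = 1: Φ(1.282 − 1.438) = 43.8%.

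| Assumed shift b | Share of implied margin | False noninferiority, one-sided 0.025 (nominal 2.5%) | Same, one-sided 0.05 (nominal 5%) | Power if the shift is against acupuncture (planned 90%) |
|---|---|---|---|---|
| 0.25 | 11–14% | 5.5% | 9.9% | 82.2% |
| 0.5 | 22–28% | 10.7% | 17.7% | 71.3% |
| 1.0 | 44–56% | 30.1% | 41.8% | 43.8% |

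These rates belong to the two-sample noninferiority comparison of change that section 2.11 presupposes. Section 2.13.1 describes a repeated-measures test of a group difference, to which they do not transfer exactly.

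**The case against.** The strongest reply is that this is a condensed article and that rater procedures usually sit in the full protocol. No section says that the psychiatrists know the allocation, watch needling or handle treatment records. Raters and acupuncturists are described separately, needles are removed after 30 minutes, and the week-24 rating falls 12 weeks after treatment ends. All of this stands. A reader might infer that the raters are known to be unblinded, and the document does not support that. It does, however, make a positive design statement: single-blind, with the subjects as the blinded party. If the raters are masked, that label misleads; if they are not, the bias is open. The text needs changing either way.

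A reader might also infer that any bias would favour acupuncture, because the authors hope for a nondrug alternative. That hope is the authors', not shown to be the raters'. The raters are psychiatrists, and the Discussion describes the comparator as standard, effective and safe. The direction is unknown.

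A third tempting reading is that the bias would consume a large part of the margin. No margin is given and the shifts are assumed. At 0.25 point the share is only 11–14%; it reaches about half only at 1 point. The error rates also suppose a true deficit equal to the margin, whereas the pilot figures slightly favour acupuncture. That boundary is the right place to examine false noninferiority, but it is not a forecast.

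Finally, not every primary outcome is exposed. The SDS is self-rated by subjects who are to be kept unaware of their group, and spectroscopy and serum measures are not scored by the psychiatrists. This limits the reach of the point but does not remove it, because the trial was sized on HAMD-17.

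**Conclusion.** The point holds as a gap in what the plan provides: blinding is stated for subjects only, and nothing masks the psychiatrists who rate HAMD-17 and the other observer-rated scales. Followed as written, the plan leaves the outcome behind the sample size open to detection bias, and training does not close that gap.

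The size cannot be fixed from the document. The calculation shows only that modest shifts would matter with an SE of 0.695: at one-sided 0.025, half a point toward acupuncture would roughly quadruple the false noninferiority rate, and one point against it would more than halve power. This rests on the assumed shifts, the assumed sidedness and, for the error rate, a true deficit at the margin. It is not an estimate of bias in this trial.

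The evidence does not extend to the CACMS statisticians. Section 2.14 has CACMS manage the data independently, and nothing on this point calls for a change there.

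**What to change.** - Amend sections 2.12 and 2.14 to state that the psychiatrists already assigned rate HAMD-17 and the other clinician-rated scales without access to allocation, treatment records (including the attendance cards) or needling sessions. Ask patients not to describe needle sites to the rater. Revise the single-blind label to match.
- Section 2.6 dates the study from May 2016 to June 2018, with follow-up into 2019, so many ratings may already exist and cannot be masked retroactively. For these, report whether the rater was masked, give a sensitivity analysis by masking status, and read HAMD-17 alongside the self-rated SDS. This describes the problem but does not remove bias already in the scores.
- State the noninferiority margin, so that the importance of any shift can be judged.

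The sample size does not change, and the cost is minor scheduling effort. No extra staff should be needed, because raters and acupuncturists are described separately. One check is needed: section 2.14 counts six psychiatrists, which fits three centres at two each (3 × 2 = 6), whereas section 2.4 lists four hospitals (4 × 2 = 8). Rater cover at the hospital that joined later should be confirmed.

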### Statistical analysis

2.13

Data analysis will be based on intention-to-treat analysis (ITT) and/or per-protocol analysis (PP) principle in the light of missing data. We will also evaluate the group effect by comparing the analysis results between the above 2 data sets to evaluate robustness of our analytical results.

All data will be analyzed using SPSS19.0 (v19.0, SPSS Inc., Chicago, IL) in the China Academy of Chinese Medical Sciences (CACMS). A *P* value <.05 will be considered as significant. Descriptive statistics will be performed with mean, standard deviation (SD), maximum, minimum, and so on by groups and time.

Baseline characteristics of patients will be summarized by groups and compared with chi-square for categorical variables, and 2-sample *t* tests (normal distributions) or Wilcoxon rank-sum test (non-normal distributions) for the continuous variables. Primary and secondary outcomes according to the measurement times are applicable to univariate repetitive measurement deviation analysis or 2-sample *t* tests, or Wilcoxon rank-sum test. If there is a violation of distribution assumption, appropriate transformation will be used.

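### In a noninferiority trial, the choice between ITT and PP is left to depend on the missing data observed, with no primary set and no rule for disagreement

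*Protocol article*

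**What the plan says.** Section 2.1 (Study design) sets the framework: "This is a multicenter, central-randomized, single-blind, sham-controlled, noninferiority clinical trial". Section 2.11 (Estimation of sample size) arrives at 84 per group and enlarges this to 104 for a predicted dropout of 20%.

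Section 2.13 (Statistical analysis) gives the rule on analysis sets: "Data analysis will be based on intention-to-treat analysis (ITT) and/or per-protocol analysis (PP) principle in the light of missing data". The sentence after it says that the group effect will also be evaluated by "comparing the analysis results between the above 2 data sets to evaluate robustness of our analytical results".

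Section 2.13 does not say which set is primary, whether noninferiority must hold in one set or both, or what is concluded if the sets differ.

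**The concern.** The rule has two weaknesses. Joining the sets with *and/or* allows ITT alone, PP alone or both as the basis of the analysis. And the stated selector is missing data, which is a feature of the observed trial and not of the design.

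This matters more under noninferiority than under superiority. Dropout and non-adherence can shrink the difference between arms, so ITT is not automatically the cautious choice. PP compares groups that are no longer protected by randomisation. Each set can err in its own direction, so neither is a safe default and the role of each has to be fixed in advance. With 20% dropout expected, the sets could differ by about 20 patients per arm, enough for one confidence limit to clear a margin and the other not.

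The article is not merely silent here. It states a rule, and an analysis plan that fixed the sets' roles would have to override it.

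**Working it through.** **Inputs.** From section 2.11: "the mean HAMD-17 scores change was 10.49 ± 4.55 after acupuncture treatment and 10.24 ± 4.46 after fluoxetine treatment"; "with 90% power, beta of 0.1, alpha of 0.05" (sidedness not given); 84 per group raised to 104; 20% dropout. The noninferiority margin is not stated. The text says only that "a clinically important difference can be detected by a sample size of at least 84 in each group".

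**1. The plan's own figures.**
- Pooled SD = √[(4.55² + 4.46²)/2] = 4.505.
- Dropout step: 84/(1 − 0.20) = 105 against the stated 104, which agrees within rounding; 104 × 0.8 = 83.2.
- The 84 cannot be reproduced directly without a margin. Solving backwards, margin = 4.505 × (z₁₋α + z₀.₉₀) × √(2/84) − assumed advantage:

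| One-sided alpha | True difference 0 | True difference +0.25 |
|---|---|---|
| 0.05 | 2.03 | 1.78 |
| 0.025 | 2.25 | 2.00 |

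These margins are implied under assumptions; none is the protocol's.

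**2. Either set may succeed, both estimating the same effect.** Assume PP is 80% of ITT (dropout taken as PP exclusion). The two test statistics then have correlation √0.8 = 0.894. P(either) = 2α − P(both):
- α = 0.025: P(both) = 0.0146; P(either) = 0.0500 − 0.0146 = 0.0354.
- α = 0.05: P(both) = 0.0314; P(either) = 0.1000 − 0.0314 = 0.0686.

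These results need no margin. They do assume that the favourable set is always taken.

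**3. Excluded patients show a smaller arm difference.** Assume 104 per arm in ITT, all with outcomes, 83 in PP and 21 excluded, with the true deficit among PP patients exactly at the margin. SE(ITT) = 4.505 × √(2/104) = 0.625. If the excluded show no difference, the ITT deficit is smaller than the margin by margin × 21/104:
- One-sided 0.025, margin 2.25: 2.25 × 21/104 = 0.454; 0.454/0.625 = 0.73; Φ(0.73 − 1.96) = 0.109.
- One-sided 0.05, margin 2.03: 2.03 × 21/104 = 0.410; 0.410/0.625 = 0.66; Φ(0.66 − 1.645) = 0.16.

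Simulation (200,000 runs, one-sided 0.025, margin 2.25, 20% excluded) gives the probability of declaring noninferiority:

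| Arm difference in excluded patients | PP | ITT | Either | Both |
|---|---|---|---|---|
| Same as the rest | 2.5% | 2.5% | 3.6% | 1.5% |
| Halved | 2.5% | 5.5% | 5.9% | 2.0% |
| Absent | 2.5% | 10.9% | 11.0% | 2.4% |

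At one-sided 0.05 and margin 2.03, *either* runs from 6.9% to 16.5% and *both* from 3.1% to 4.8%.

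In the lower two rows the ITT effect truly lies inside the margin, so those declarations are false with respect to the effect in PP patients.

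**4. Power cost of requiring both sets.** Take one-sided 0.025, margin 2.25 and true difference 0. SE(PP) = 4.505 × √(2/83) = 0.699.
- ITT: Φ(2.25/0.625 − 1.96) = 0.95.
- PP: Φ(2.25/0.699 − 1.96) = 0.90.
- Both, with correlation √(83/104) = 0.893: 0.89.

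Requiring both therefore costs about one percentage point against PP alone.

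**The case against.** A reader might infer that only one set will be analysed and that the sponsor will keep the one that succeeds. The article does not support that. Comparing the sets for robustness requires both to be run, and the stated trigger is missing data, not the result. Nor does the article say when the choice is made or that results would be known by then; section 2.14 gives data management to an independent third party, although no blinded review is described. If the choice followed only the amount of missing data, unrelated to outcome, and both sets estimated the same effect, the inflation in step 2 would not arise. These points stand, and they make 3.5% and 6.9% ceilings for that case, not what the rule itself produces.

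A reader might also judge dilution against a 2-point margin: a deficit of 2.25 among completers becomes 2.25 × 0.8 = 1.8 in ITT, apparently inside it. That margin is nowhere in the article, and noninferiority is decided on a confidence limit. With SE 0.625, a true deficit of 1.8 would pass a margin of 2.0 with probability Φ(0.2/0.625 − 1.96), about 5% at one-sided 2.5%, or about 9% at one-sided 5%.

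The detailed PP definition is ordinary analysis-plan content, so its absence from a condensed article is no fault. Requiring success in both sets is also only one convention; one primary set named in advance, with the other as sensitivity analysis, would remove the ambiguity too.

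None of this answers the narrower point: the text makes the basis of the conclusion conditional on observed missingness and gives no rule for discordant results.

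**Conclusion.** The concern holds in this form: section 2.13 lets observed missing data determine which set carries the noninferiority conclusion, names no primary set and has no rule for disagreement. That follows from the wording and needs no calculation.

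The size is conditional. With PP at 80% of ITT, equal effects in both sets and the favourable set always taken, one-sided error is at most about 3.5% instead of 2.5%, or 6.9% instead of 5%. If the excluded 20% show no arm difference, ITT alone would declare noninferiority about 11% of the time at one-sided 2.5%, given an assumed margin near 2.25 and a deficit among PP patients exactly at it. Margin, sidedness and the behaviour of excluded patients are assumptions.

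The article does not show that results will be picked after the fact. The verdict is also not yet fully defined for either set, because no margin or confidence-interval rule is stated and section 2.13.1 describes a test for a difference between groups. This should be fixed, but it falls short of a fault that invalidates the trial.

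**What to change.** In section 2.13, delete the clause that joins the sets with *and/or* and ties the choice to missing data. State instead that ITT and PP will always both be analysed, with their roles fixed before unblinding. The preferred rule is that noninferiority is claimed only if the confidence limit lies inside the prespecified margin in both sets, and that any superiority claim rests on ITT. If the sponsor prefers a single primary set, name it now and say how a discordant result in the other will be interpreted.

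The cost is a sentence or two and slightly lower power (about 89% against 90% for PP alone, under the assumptions in step 4). No change to sample size or treatment follows. The rule cannot be applied until a margin and the sidedness of the interval are stated, so these must be added at the same time.
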